## Withdrawal of consent for further data collection

The participant withdraws consent for further follow-up visits and recording of clinical data. They maintain consent for blood and fluid samples already taken to be analysed, and for data already collected to be used in analyses.

## Withdrawal of consent for further data collection and use of existing data

The participant withdraws consent to further follow-up visits, recording of clinical data and the use of any clinical data already collected. They maintain consent for blood and fluid samples already taken to be analysed.

## Withdrawal of consent for sample analysis

The participant withdraws consent for existing blood and pleural fluid samples to be analysed, and for any data already obtained from these samples to be used in the final analysis. Samples and associated data should be destroyed in line with local policy. They maintain consent for ongoing trial follow-up, data collection and the use of this data in the final analysis.

## Loss to follow up

Loss to follow up will be minimised by diligent liaison with the patient, their oncology team and general practitioner (GP). Any loss to follow-up should be recorded on the participant withdrawal/loss to follow-up form. For participants moving from the area, every effort should be made for the participant to be followed up at another centre, or for follow up via their GP.

# ADVERSE EVENT MONITORING

## Definitions

*Adverse Event (AE)*

Adverse Events (AEs) are any untoward medical occurrence in a patient or clinical trial subject administered an investigational medicinal product (IMP), medical device or intervention and which does not necessarily have a causal relationship with this treatment. This includes any unfavourable and unintended signs, including abnormal laboratory results, symptoms or a disease temporarily associated with an investigational product.

AE must always be recorded on an eCRF and in the patient's medical notes.

*Adverse Reaction (AR)*

Adverse Reactions (ARs) are adverse events where there is evidence to suggest there is a causal relationship between the event and the IMP.

*Serious Adverse Event (SAE) or Serious Adverse Reaction (SAR)*

Serious Adverse Events (SAEs) are defined as any untoward medical occurrence(s) that results in:

- death
- real and immediate threat to life
- hospitalisation
- prolongation of existing hospitalisation
- persistent or significant disability or incapacity
- a congenital anomaly or birth defect
- other health event which in the opinion of the clinician is serious

*Serious Adverse Reaction (SAR)*

Any SAE that is classed as serious in nature and which is consistent with the information about the IMP set out in the summary of product characteristics (SmPC) for that product or listed as an expected reaction in the trial protocol.

*Suspected Unexpected Serious Adverse Reaction (SUSAR)*

Any SAE/SAR that is suspected to be caused by the IMP, but which is not consistent with the information available about the IMP set out in the SmPC for that product or listed as an expected reaction in the trial protocol. If the event is not listed as expected, or has occurred in a more serious form than anticipated, it should be considered a SUSAR.

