## Causality

The relationship between the trial treatment and the adverse event will be graded as one of the following:

- Unrelated – Temporal relationship of the onset of the AE, relative to the administration of the product, is not reasonable or another cause can explain the occurrence.
- Unlikely – Temporal relationship of the onset of the AE, relative to the administration of the product, is likely to have another cause which can by itself explain the occurrence
- Possibly related – Temporal relationship of the onset of the event, relative to administration of the product, is reasonable but the even could have been due to another, equally likely cause.
- Probably related – Temporal relationship of the onset of the event, relative to administration of the product, is reasonable and the event is more likely to be explained by the product than any other cause.
- Definitely – Temporal relationship of the onset of the event, relative to administration of the product, is reasonable and there is no other cause to explain the event, or a re-challenge (if feasible) is positive.
- Not assessable - there is insufficient or incomplete evidence to make a clinical judgement of causality.

Any event that is assessed as possibly, probably or definitely related should be classified as an AR.

The assignment of causality to an adverse event or adverse reaction should be made by the investigator responsible for the care of the participant based on the definitions above. If any doubt about causality exists, the local investigator should inform the Trial Manager or Chief Investigator. The pharmaceutical company and/or other clinicians may be asked to advise in some cases. If there is disagreement regarding causality, the involved parties will discuss the case together. In the event that no agreement is reached, the MHRA will be informed of both points of view.

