## Adverse events in TILT and ASSESS-meso participants

Adverse event data is collected at every visit, for all participants in ASSESS-meso and TILT. Whilst participants in ASSESS-meso will not experience any adverse reactions (AR) since they have not received an intervention, it is nonetheless possible that they may experience AEs or SAEs.

Although ASSESS-meso participants are not considered CTIMP participants, some will nonetheless be contributing ‘control’ data to the TILT trial. For clarity and transparency of reporting, all SAEs occurring in ‘control’ participants will be reported to the sponsor in accordance with the specifications below.

Furthermore, because TILT participants will return to follow up in ASSESS-meso following the end of trial, ongoing adverse events monitoring is required in case of any late adverse reactions that present after the 3 month trial period. Reporting of these adverse events will comply with the reporting procedure outlined below. In addition, trial-specific protocol 6b (TSP06b) will contain information on potential adverse reactions to OK432 and BCG, and advice on appropriate management. This TSP will continue to be available for TILT participants once they have returned to ASSESS-meso following the end of trial.

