## Reporting procedures

All adverse events will be recorded in the patient’s medical notes and on eCRFs. Depending on the nature of the event the reporting procedures below should be followed. Any questions concerning adverse event reporting should be directed to the trial coordination centre in the first instance.

*Non-serious AE/AR*

All such toxicities, whether expected or not, should be recorded in the adverse events section of the relevant eCRF and on a separate adverse event log for each participant. Non-serious AE/AR do not need to be reported to the trial coordination centre.

*Expected AE*

Expected AE, as listed in section 12.2, should be recorded on the appropriate eCRF and on a separate adverse event log as above. These events do not need be reported as SAE (even if the criteria for such are met) unless the local Principal Investigator deems this necessary.

*Expected AR*

There are a number of expected AR related to both IMPs, including fever, tachycardia, tachypnoea and chest pain following administration. Non serious AR should be recorded on the appropriate eCRF and on a separate adverse event log as above. Serious AR, even if expected, should be reported to the trial coordinating centre and the sponsor in accordance with the specifications below.

*SAR/SAE*

In the case of SAE or SAR, an SAE form (Initial Safety Report Form, I/QMS/SOP/013a) should be completed and faxed/emailed to the trial coordination centre and to the sponsor within 24 hours. The SAE form asks for nature of event, date of onset, severity, corrective therapies given, outcome and causality (as detailed in sections 12.3 and 12.4).

The Principal Investigator should review all SAE forms, and state expectedness and relatedness to the trial. All forms must be signed by the PI (submission of the form by email from the PIs professional address will act as PI signature). Receipt of the form will be reviewed by a delegated member of North Bristol NHS Trust Research and Innovation Department (R&I) and logged on the R&I database. The report may be reviewed by a meeting of members of R&I and a clinical trial pharmacist may be consulting along with the CI, if deemed necessary.

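### Section 12.1 defines a serious adverse reaction by whether the event is listed, not by causality, which contradicts the rest of section 12 and leaves SAR classification inconsistent.

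*Protocol*

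**What the plan says.** Section 12.1 (Definitions) gives the SAR entry as "Any SAE that is classed as serious in nature and which is consistent with the information about the IMP", continuing "set out in the summary of product characteristics (SmPC) for that product or listed as an expected reaction in the trial protocol". An event must be serious and must be listed. Nothing in the sentence asks whether the product caused it.

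The surrounding text uses a different idea of a reaction:

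- **AR, section 12.1:** "Adverse Reactions (ARs) are adverse events where there is evidence to suggest there is a causal relationship between the event and the IMP".
- **SUSAR, section 12.1:** "Any SAE/SAR that is suspected to be caused by the IMP, but which is not consistent with the information available about the IMP".
- **Section 12.2 (Expectedness):** expected ARs are included within all ARs, and ARs that meet the SAR criteria go to the sponsor.
- **Section 12.3 (Causality):** "Any event that is assessed as possibly, probably or definitely related should be classified as an AR".
- **Section 12.4 (controls):** "participants in ASSESS-meso will not experience any adverse reactions (AR) since they have not received an intervention". Serious events in controls are reported as SAEs.
- **Section 12.5 (Reporting procedures):** "There are a number of expected AR related to both IMPs, including fever, tachycardia, tachypnoea and chest pain following administration". Serious ARs are to be reported even when they are expected.

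**The concern.** Two separate questions are asked of a serious event: did the product cause it, and was it foreseeable from the reference safety information? The first separates a SAR from an SAE. The second separates an expected SAR from a SUSAR. The SAR sentence in section 12.1 puts the second question in place of the first.

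This could matter in practice because the listed reactions overlap with the disease. Chest pain and breathlessness are followed as symptoms in every participant, and section 12.2 expects many adverse events to arise from the malignancy itself. Two sites applying different sentences of section 12 to the same admission could label it differently. Adverse events are a secondary outcome in the Study design section, and SARs are a category that the trial steering committee, acting as data monitoring committee, reviews under section 16.4.

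**Working it through.** The protocol gives no figure on this point, so the check sets its rules side by side. Take a serious event in a dosed participant and apply the SAR sentence in section 12.1 and the causality rule in section 12.3.

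| Listed? | Causality grade | SAR by 12.1? | AR by 12.3? | Result |
|---|---|---|---|---|
| Yes | Possibly, probably or definitely related | Yes | Yes | Consistent |
| Yes | Unrelated or unlikely | Yes | No | Contradiction: a SAR that is not an AR |
| No | Possibly, probably or definitely related | No | Yes | Contradiction: a serious AR that is not a SAR, although it is a SUSAR |
| No | Unrelated or unlikely | No | No | Consistent |

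The rules disagree in two of the four cells, the two where listing and causality point in different directions.

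Three other texts show which meaning was intended:

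1. The SUSAR definition starts from any SAE/SAR and then requires that the event is not consistent with the product information. Under the SAR sentence just above it, every SAR is consistent with that information, so no SAR could ever become a SUSAR. The SUSAR wording makes sense only if a SAR can be unlisted.
2. Section 12.2 speaks of all ARs, including expected ones, and section 12.5 of serious ARs even if expected. Both make expected reactions a subset of reactions, so a serious reaction may also be unexpected.
3. Section 12.1 first introduces SAE and SAR under a joint heading with one list of seriousness criteria. What should then distinguish a SAR is the word reaction, which the same section defines causally.

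For a control with, say, fever or chest pain, the SAR sentence taken alone might seem to apply. Section 12.4 settles the matter: no ARs in participants who received no intervention, and their serious events are SAEs. The reactions in section 12.5 are also described as following administration, which an undosed control has not had.

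**The case against.** The strongest reply is that this is loose drafting which the rest of section 12 repairs. A reaction is defined causally a few lines earlier, every event is graded for causality, and sections 12.2 and 12.5 use SAR in the conventional sense. SAEs and SARs share one form and one 24-hour limit. That form records causality, and the principal investigator states relatedness and expectedness, so a correct table could always be rebuilt. Section 16.4 puts all SAEs, SARs and SUSARs before the steering committee and sets no SAR count as a stopping threshold. Most of this stands, and it limits the consequence. It does not remove the contradiction: the one sentence headed as the SAR definition still gives a different answer in two of four cases.

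Four stronger readings are tempting, and the protocol does not support them.

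- **SARs would be counted in controls.** Section 12.4 rules this out.
- **Related but unlisted serious events would be lost.** The SUSAR definition captures them, and section 12.5 gives them the stricter, expedited route.
- **Every SAR escapes reporting, because section 12.5 exempts expected SAE/SARs and section 12.1 makes every SAR expected.** The exemption refers back to section 12.2, whose itemised expected events all concern the underlying malignancy. Sections 12.2 and 12.5 both require serious ARs to be reported even if expected. The exemption wording still has to be reconciled with them.
- **The chance of a false SAR can be calculated.** With 4 per arm and an assumed proportion p with an unrelated serious event of a listed type, 1 − (1 − p)^4 gives 34%, 59% and 76% for p = 10%, 20% and 30%. The protocol gives no value for p. The sum also assumes that every such event is coded as a SAR despite an unrelated grade on the same form, and it ignores that section 12.2 already treats malignancy-related admissions as expected AEs. The protocol defines no SAR rate per arm, so these figures do not measure the defect.

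**Conclusion.** The concern holds as an internal contradiction in a safety definition. Section 12.1 defines a SAR by seriousness and listing. The AR and SUSAR definitions beside it, and sections 12.2, 12.3 and 12.5, require or presuppose a causal definition with expectedness as a separate attribute.

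Its effect is confined to how serious events in dosed participants are labelled and tabulated: listed events graded unrelated or unlikely may be counted as SARs, and related unlisted events may be left out of a SAR count while appearing as SUSARs. How often this would happen depends on which sentence a site applies and on event rates that the protocol does not give, so no size can be stated. The label does not decide whether an event falls within the steering committee's remit.

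It is worth correcting because the SAR category is reviewed by the oversight committee and the correction is almost free.

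**What to change.** In section 12.1, define a SAR as an AR, meaning an event graded possibly, probably or definitely related under section 12.3, that meets at least one of the seriousness criteria, whether or not it is listed. Use the SmPC and the protocol's list of expected reactions only to divide SARs into expected SARs and SUSARs. State that SARs will be tabulated on that definition.

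Then read sections 12.2 to 12.5 against the new definition. In particular, reconcile the section 12.5 exemption for expected SAE/SARs with the statements in sections 12.2 and 12.5 that serious ARs are reported even if expected.

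The cost is a few sentences. Causality and expectedness are already stated when an SAE is reported, so no extra data collection is needed.

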## Expectedness

The population of patients involved in TILT is one in which a high number of adverse events are expected. Many of these will unrelated to IMP administration or trial-related procedures, but rather will be a direct consequence of the patient’s underlying malignancy. These expected AE do not need to be reported to the sponsor, even if they meet the criteria for an SAE.

Expected adverse events in these settings are:

- Death due to underlying malignancy
- Admission related to underlying malignancy
- Prolongation of inpatient hospital stay due to underlying malignancy

In addition to these expected AE, there are a number of AR that are well documented and regarded as normal reactions following intra-pleural OK432 or BCG administration. However, because neither IMP has been used in this context in this country before, and because TILT is a feasibility trial, all AR, including expected AR must be reported on eCRFs and, if they meet the criteria for SAR, should be reported to the sponsor in accordance with the guidance below.

## Causality

The relationship between the trial treatment and the adverse event will be graded as one of the following:

- Unrelated – Temporal relationship of the onset of the AE, relative to the administration of the product, is not reasonable or another cause can explain the occurrence.
- Unlikely – Temporal relationship of the onset of the AE, relative to the administration of the product, is likely to have another cause which can by itself explain the occurrence
- Possibly related – Temporal relationship of the onset of the event, relative to administration of the product, is reasonable but the even could have been due to another, equally likely cause.
- Probably related – Temporal relationship of the onset of the event, relative to administration of the product, is reasonable and the event is more likely to be explained by the product than any other cause.
- Definitely – Temporal relationship of the onset of the event, relative to administration of the product, is reasonable and there is no other cause to explain the event, or a re-challenge (if feasible) is positive.
- Not assessable - there is insufficient or incomplete evidence to make a clinical judgement of causality.

Any event that is assessed as possibly, probably or definitely related should be classified as an AR.

The assignment of causality to an adverse event or adverse reaction should be made by the investigator responsible for the care of the participant based on the definitions above. If any doubt about causality exists, the local investigator should inform the Trial Manager or Chief Investigator. The pharmaceutical company and/or other clinicians may be asked to advise in some cases. If there is disagreement regarding causality, the involved parties will discuss the case together. In the event that no agreement is reached, the MHRA will be informed of both points of view.

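### The causality grades in section 12.3 are not mutually exclusive: *Unrelated* also takes in events that meet *Possibly* or *Probably related*, across the adverse-reaction boundary

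*Protocol*

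**What the plan says.** Protocol section 12.3 (Causality) lists six grades and requires one per event. Those that matter here are:

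- *Unrelated*: the timing "is not reasonable or another cause can explain the occurrence".
- *Unlikely*: the timing "is likely to have another cause which can by itself explain the occurrence".
- *Possibly related*: the timing "is reasonable but the even could have been due to another, equally likely cause".
- *Probably related*: reasonable timing, and "the event is more likely to be explained by the product than any other cause".
- *Not assessable*: "there is insufficient or incomplete evidence to make a clinical judgement of causality".

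The boundary rule follows: "Any event that is assessed as possibly, probably or definitely related should be classified as an AR". The local investigator assigns the grade. If there is doubt about causality, the Trial Manager or Chief Investigator is to be told, and an unresolved disagreement goes to the MHRA with both views.

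Section 12.1 defines an AR as an event with evidence pointing to a causal link with the product, and makes SUSAR status depend on suspected causation. Section 12.2 (Expectedness) states that "The population of patients involved in TILT is one in which a high number of adverse events are expected" and attributes many of them to the malignancy. It still requires every AR to be reported on the eCRF, because neither agent has been used in this setting in the UK.

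**The concern.** A scale from which exactly one grade must be chosen works only if the grades do not overlap, above all at the point where a consequence changes. Here the overlap lies on that point. One of the competing grades makes the event an AR and opens the route to SAR or SUSAR status; the other does not.

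The population makes this more than a drafting curiosity. Participants have mesothelioma and an indwelling pleural catheter, so for many events after OK432 or BCG the disease or the catheter is a candidate explanation. An investigator who reads *Unrelated* literally can use it whenever such an explanation is available, even if the product is at least as likely. At stake is the consistency of AR and SUSAR labels across three hospitals. Adverse events are a listed secondary outcome, and the results are meant to inform whether one or both agents go forward.

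**Working it through.** No rate, power or sample size is involved, so the check is a decision table. The inputs are the definitions in section 12.3. Timing is either reasonable or not. When it is reasonable, the other cause is absent, less likely than the product, equally likely, or more likely.

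| Timing | Other cause | Grades literally met | AR? |
|---|---|---|---|
| Reasonable | None | *Definitely* | Yes |
| Reasonable | Less likely than product | *Probably* and *Unrelated* | Yes and no |
| Reasonable | Equally likely | *Possibly* and *Unrelated* | Yes and no |
| Reasonable | More likely | *Unlikely* and *Unrelated* | No |
| Not reasonable | Any | *Unrelated* applies | No |

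1. An equally likely cause is one that can explain the event. Every event meeting *Possibly related* ("could have been due to another, equally likely cause") therefore also meets the second limb of *Unrelated*.
2. *Probably related* compares the product with any other cause, so it allows a less likely one to exist. If that cause can explain the event, *Unrelated* is met again.
3. With reasonable timing, 2 of the 4 states fall on both sides of the AR boundary.
4. *Unlikely* and *Unrelated* also overlap, although both are non-AR grades. The *Unlikely* sentence is garbled: its grammatical subject is the temporal relationship, not the event.
5. *Not assessable* is absent from the AR rule, and no handling is stated for it.

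Next, what depends on the label (sections 12.2, 12.5 and 16.4). All adverse events go on the eCRF. Serious events go to the coordinating centre and sponsor within 24 hours whatever the grade, except death, admission or prolonged stay attributed to the malignancy. The Trial Steering Committee reviews all SAEs, SARs and SUSARs. Non-serious events need not be reported to the coordinating centre. The grade therefore governs the AR label and, in practice, SUSAR classification with its 7- or 15-day reporting. It does not govern whether the event is recorded.

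The documents give no event rates or grading frequencies, so an under-count cannot be sized. For scale only, with 4 participants per agent and assuming all are treated, moving one participant from AR to non-AR shifts that arm's AR proportion by 1/4 = 25 percentage points, or the combined proportion by 1/8 = 12.5 points. That would be true of any misclassification in arms this small.

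**The case against.** The strongest reply is that the scale is plainly ordered and has a grade written for the equally likely case. A sensible investigator who judges two causes equally likely will choose *Possibly related*, and nothing directs them to *Unrelated*. Section 12.5 also names fever, tachycardia, tachypnoea and chest pain as expected reactions to both products. Section 9.4 requires deaths, systemic sepsis and pleural infection to be recorded specifically. Doubt is escalated, and the principal investigator reviews every SAE form.

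Much of this stands, and it rules out several stronger readings that a reader might infer:

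- *Such events must be graded Unrelated.* They meet two grades, and the more specific one is an AR. The fault is ambiguity, not forced misgrading.
- *Reactions are under-counted.* This is a possible direction of bias, not a demonstrated result, and the events are still recorded.
- *Not assessable events are never treated as reactions.* The protocol is silent. SUSAR status rests on suspicion rather than on a listed grade, and later information must be forwarded.
- *The 25-point figure measures the problem.* It is only one participant in four.

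The reply does not close the gap. Escalation depends on the investigator feeling doubt, and one applying the literal *Unrelated* wording need feel none. Non-serious events, which include many of the expected reactions, have no stated prompt central check of their grade. The reporting exemption for events attributed to malignancy also applies where an alternative cause is most readily available, although it turns on that attribution and not on the causality grade.

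**Conclusion.** The point holds as a defect in a stated rule. *Unrelated* overlaps *Possibly related* in every case, and *Probably related* wherever a less likely alternative can explain the event. The overlap straddles the AR boundary, so the same event can be classified either way in compliance with the protocol. The likely direction, if there is one, is towards fewer AR and SUSAR labels. That rests on the assumption that some investigators will apply the wording literally in patients whose malignancy is nearly always an available explanation. The size is unknown and cannot be derived from the document. Feasibility, the primary outcome, is unaffected because its thresholds do not use AR rates.

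The silence on *Not assessable* is secondary. Counting such events as reactions by default would be a policy choice that no section makes, and it would sit awkwardly with the section 12.1 definition, which asks for evidence of a causal link.

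**What to change.** In section 12.3:

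1. Redefine *Unrelated* as: timing not reasonable, or another cause established with no reasonable possibility that OK432/BCG contributed.
2. Reword *Unlikely* with the event as its subject: timing reasonable, another cause more likely than the product, and a contribution from the product not excluded.

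Re-running the table with these definitions gives one grade per row. With reasonable timing, no other cause is *Definitely*, a less likely one *Probably*, an equally likely one *Possibly*, and a more likely one *Unlikely*. An established cause with contribution excluded is *Unrelated*, as is unreasonable timing.

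3. As a secondary change, state how a serious *Not assessable* event in someone who received OK432 or BCG is handled until it can be graded, and reconcile that with the AR definition in section 12.1. The choice of rule is for the sponsor.

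The cost is two or three sentences and matching guidance for the SAE form. The downside is small: a few more events may be classed as reactions. No treatment rule or visit changes.
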